## Patient Completion and Withdrawal

### For each patient, according to the protocol, the study is deemed

- **Completed**

The patient will be administered study treatment as per the protocol, and completes all the safety and efficacy assessments on- Day 7, Day 30, Day 45 (only for patients with splenic aspirate score +1 on Day 30), and at 6 months after study drug administration.

- **Discontinued/withdrawn**- Withdrawal from the study can occur under the following circumstances:
  - 1. Death
    2. Adverse event
    3. Lack of efficacy (treatment failure)
    4. Patient consent withdrawal
    5. Investigator’s discretion
    6. Sponsor’s decision
    7. Pregnancy in a patient
    8. Lost to follow-up*

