**Study Treatment:**

- 1. Investigational drug - Amphomul^®^ (Amphotericin B Emulsion manufactured by Bharat Serums and Vaccines Ltd.), and
  2. Comparator drug - AmBisome (manufactured by Gilead Sciences, Inc.)

**Dosage and route of administration:** On the basis of Phase II study results (BSV‑AMBE II‑KA-0706), dose of Amphomul^®^ was decided for this Phase III study. Patients will be randomized to receive either infusion of Amphomul^®^ 15 mg/kg as a single dose administered over 4 to 6 hours or AmBisome 15 mg/kg administered as a single dose infusion over 4 to 6 hours.

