### Procedures for handling patients who discontinue the study prematurely

Investigators should make an attempt to contact those patients who do not return for follow-up on Day 30, Day 45 (only for patients with splenic aspirate score +1 on Day 30) and 6 months after study drug administration. Information gathered should be described in the source and CRF.

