### Recording Patient Withdrawals

In the event of a patient withdrawal, the following information must be recorded in the CRF:

- Date of withdrawal
- Reason for withdrawal
- Last treatment date
- Follow-up assessments

If a patient withdraws or is withdrawn from the study, he/she will be requested to return for a follow-up visit after 1 week of the withdrawal date, for recording AEs and physical examination.

The Investigator should continue to follow-up all SAEs or other AEs that are considered to be related to the study drugs, until resolved or assessed to be chronic or stable by the Investigator. This should be documented in the patient’s medical records. This follow‑up may be extended beyond the end of the study period.

In the case of patients lost to follow-up, all attempts to contact the patient must be documented in the patient’s medical records.

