**Visit 1-(Day 1 to Day 7)**

**Visit 1 - Day 1 (Start of study drug treatment)**

- The patients will be re-evaluated clinically.
- If all eligibility criteria are satisfied, then the patient will be included in the study to receive treatment with Amphomul^®^ or AmBisome.
- Patients not fulfilling any of the eligibility criteria on this visit would not be included in the study and labeled as screening failures.
- Laboratory investigations will be done at Investigator’s discretion.
- Permuted Block randomization with block of size 4 and ratio of 3:1 in the two groups (Amphomul and AmBisome) will be generated for each center. Patients will be randomized in the ratio of 3:1 to receive either Amphomul^®^ infusion (15 mg/kg as a single dose infusion) over 4 to 6 hours or AmBisome 15 mg/kg as a single dose infusion over 4 to 6 hours.
- Test dose consisting of 1 mg will be administered in 5% dextrose over a period of approximately 15-20 minutes prior to administration of full-dose infusion of Amphomul^®^.
- The IP (Amphomul^®^)*,* diluted (maximum dilution allowed to 1 mg/mL) in 5% dextrose will be administered as an infusion.
- Before administration AmBisome has to be diluted with 12 mL sterile water to yield a preparation containing 4 mg of Amphotericin B/mL. This diluted AmBisome will be further diluted with 5% Dextrose to a concentration not less than 1 mg/mL.
- Test dose consisting of 1 mg will be administered in 5% dextrose over a period of 10 minutes prior to administration of full-dose infusion of AmBisome
- No premedication will be administered prior to the study drug administration.
- However, if patient experiences chills or any infusion related reactions after starting infusion, concomitant medication(s) can be administered at the discretion of the investigator.
- As for use of all Amphotericin B products, facilities for cardiopulmonary resuscitation will be kept readily at hand when administering the drug due to possible occurrence of anaphylactic reactions.
- In case of severe hypersensitivity reactions uncontrolled by the premedications or cardiopulmonary complications of hypersensitivity, the patient would be discontinued from the study and would be treated for the complications till the patient becomes stable.
- The patient will be closely monitored for approximately 6 hours following the completion of infusion for any IRTs.
- Vital signs will be recorded.

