## Dosing schedule and Administration

### Investigational product (Amphomul^®^)

- Amphomul^®^ shall be administered by IV route at the site of appropriate IV access. It can also be administered into the central venous catheters, if appropriate. The drug should be administered as a slow IV infusion.
- The Investigator or designee will be required to withdraw Amphomul^®^ from the vial(s), and administer each patient the dose specified as slow IV infusion.
- Before administration, Amphomul^®^ will be diluted to 1 mg/mL in 5% dextrose.
- Test dose consisting of 1 mg will be administered in 5% dextrose over a period of approximately 15-20 minutes prior to administration of full-dose infusion of Amphomul^®^.
- The IP (Amphomul^®^)*,* diluted (maximum dilution allowed to 1 mg/mL) in 5% dextrose will be administered as a slow IV infusion over 4 to 6 hours.
- As for use of all Amphotericin B products, facilities for cardiopulmonary resuscitation will be kept readily at hand when administering the drug due to possible occurrence of anaphylactic reactions.
- The patients will be observed for 6 hours following the end of infusion, with appropriate medical treatment readily available in case of a rare anaphylactic reaction during the administration of infusion. Reactions that occur during this time must be recorded by the Investigator in the CRF.
- In case of any toxicity due to study drug, patient will be withdrawn from the study as per investigator’s discretion

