# 16. CONCURRENT THERAPY

At each study visit, the PI should question the patient/LAR/impartial witness about any medication taken. Concomitant medications are not expected to interfere with study drug administration during the study, unless they lead to clinically significant impairment of the renal function (nephrotoxic drugs such as aminoglycosides).

In case of any IRTs the patient would be administered Tab Acetaminophen 500 mg or Tab Pheniramine 25 mg or injection paracetamol/pheniramine maleate (or any other concomitant medication as per investigator’s discretion) as concomitant medications.

In case of severe hypersensitivity reactions uncontrolled by the above mentioned medications or cardiopulmonary complications of hypersensitivity, the patient would be discontinued from the study and would be treated for the complications appropriately.

Any other concomitant medication administered must also be recorded in the CRF with generic name and/or trade name of the medication, start and end dates of treatment.

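### A patient who has had the full single Day 1 infusion can still be withdrawn from the study for non-efficacy reasons, and nothing then requires the Day 30/45 and 6-month cure assessments

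*Protocol*

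**What the plan says.** **Treatment.** The Study Summary gives each drug at 15 mg/kg, "administered as a single dose infusion over 4 to 6 hours", on Day 1. After that there is no study drug left to stop.

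**Withdrawal.** Section 12.6.1 says "Withdrawal from the study can occur under the following circumstances" and lists eight reasons. Four of them (adverse event, investigator's discretion, sponsor's decision, pregnancy) do not in themselves settle the cure outcome or prevent its collection. What ends is study participation, not drug. Three other places add to this:
- Section 13, Visit 1 - Day 1, on severe hypersensitivity: "the patient would be discontinued from the study and would be treated for the complications till the patient becomes stable".
- Section 16, on the same event: "the patient would be discontinued from the study and would be treated for the complications appropriately".
- Section 15.6.1 (Amphomul): "In case of any toxicity due to study drug, patient will be withdrawn from the study", at the investigator's discretion. Section 15.6.2 (AmBisome) has no such bullet.

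**After withdrawal.** Section 12.6.3 asks for a visit "after 1 week of the withdrawal date, for recording AEs and physical examination". Sections 18.2.3 and 18.3.5 add re-evaluation within 2 weeks if an adverse event is present, and Section 18.3.1 continues adverse event recording. Section 12.6.2 says "Investigators should make an attempt to contact those patients who do not return" at Day 30, Day 45 or 6 months, and "Information gathered should be described in the source and CRF".

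**Outcome.** Section 20.2.2 tests non-inferiority on definitive cure in MITT and PP. Under Section 20.1, MITT needs drug given for the protocol-specified duration and at least one efficacy assessment; PP needs completed study visits.

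**The concern.** In a multi-dose trial, leaving treatment and leaving the study are easily run together. Here dosing is over within hours on Day 1, so an adverse event on Day 5 or a pregnancy in month 3 gives no reason to stop finding out whether the patient was cured.

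The primary comparison needs initial cure at Day 30 or 45 and freedom from relapse to 6 months. If a fully dosed patient leaves for a reason that is discretionary or linked to toxicity, in a trial where investigator and patient know the arm (Section 15.3), the loss may be related to outcome. MITT and PP share the weakness, so neither checks the other. The allowance of close to 20% in Section 11.2 protects patient numbers, not comparability. A statistical analysis plan can set how a missing outcome is counted, but it cannot recover one that was never collected.

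**Working it through.** **1. Which patients are affected.**
- *Treatment failures* (aspirate above +1 at Day 30, or +1 and above at Day 45): outcome known. Not affected.
- *Infusion stopped for intolerance or a DLT*: Section 17.2 gives a status, failure or non-evaluable. Not the main gap.
- *Full infusion given, then withdrawn for adverse event, discretion, sponsor's decision or pregnancy*: Section 17.2 does not apply, because no treatment was discontinued, and no section keeps the cure assessments. This is the gap.

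Within the third group, Section 17.2 puts the first efficacy assessment at Day 30. A patient withdrawn earlier therefore has none scheduled and drops out of MITT. One withdrawn after Day 30 can stay in MITT with no 6-month outcome. Both leave PP.

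**2. The plan's own figure.** 400 / (1 - 0.20) = 500, which at 3:1 is 375 and 125. This reproduces Section 11.2. The protocol states no cure rate. With a one-sided 0.025 level and margin 0.10, 80% power needs 412 evaluable patients in total at a cure rate of 0.89 in both arms and 380 at 0.90. The planned 400 thus fits about 0.89 to 0.90, and the assumed rates of 90% and 95% below are reasonable for illustration.

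**3. Weight of one missing outcome.** 1/375 = 0.27 point (Amphomul); 1/125 = 0.80 point (AmBisome).

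**4. Range left open.** Let a share x of each arm have no outcome. Each cure proportion lies between its value with the missing counted as not cured and that value plus x. The difference therefore lies within x either side of its value with all missing counted as not cured.
- x = 1% (3.75 and 1.25 patients, so about 4 and 1): 1 point either way.
- x = 4% (15 and 5 patients): 4 points either way.

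The margin is 10 points. These shares are assumptions. The extremes need every lost patient cured in one arm and none in the other.

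**5. Bias if the lost are excluded.** The shift in one arm is (share lost) x (cure rate in those kept minus cure rate in those lost). With 5% lost, 95% cure in those kept and 50% to 70% in those lost (all assumed): 0.05 x (0.95 - 0.70) = 1.25 points to 0.05 x (0.95 - 0.50) = 2.25 points of overstatement. Which treatment this favours depends on the arm in which it happens.

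**6. Power.** Wald interval, equal true cure p, power = Phi(0.10/SE - 1.96), loss equal in both arms.

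| Case | n | Half-width, p = 0.90 / 0.95 (points) | Power, p = 0.90 / 0.95 |
|---|---|---|---|
| No loss | 375, 125 | 6.07 / 4.41 | 0.90 / 0.99 |
| 4% lost, counted not cured (proportion 0.96p) | 375, 125 | 6.94 / 5.73 | 0.81 / 0.93 |
| 4% lost, excluded | 360, 120 | 6.20 / 4.50 | 0.89 / 0.99 |

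The table starts from all enrolled patients, not the 300 and 100 planned as evaluable, to isolate the effect of this one source of loss. Power stays above 0.80 throughout, so the issue is possible bias.

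**The case against.** Section 12.6.1 is permissive: it lists reasons for leaving and directs nobody to withdraw a fully dosed patient. Much toxicity around the infusion is dealt with elsewhere, by temporary interruption (Sections 11.5 and 15.6.4) or by a status in Section 17.2. Some exits are hard to avoid: a sponsor's decision may mean study termination, and pregnancy bears on a repeat splenic aspirate. Section 12.6.2 names the right visits and requires what is learned to be recorded. As the 6-month assessment is clinical unless relapse is suspected, contact then could yield relapse information for a patient who already has initial cure. The affected group may be a handful, and how missing outcomes are counted is properly left to the analysis plan.

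Most of this stands, and it narrows the point to fully dosed patients, with the widest gap before Day 30. It does not close the gap. Section 12.6.2 asks for contact attempts with patients who do not return and schedules no aspirate or cure assessment. The follow-up assessments listed in Section 12.6.3 are an item to record in the CRF, not a visit schedule.

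A reader might infer that withdrawn patients are abandoned. They are not: safety follow-up and contact attempts are specified. A reader might also infer, from the toxicity bullet standing only in the Amphomul section, that the plan tilts the result towards Amphomul. The documents do not support that: Section 12.6.1 already allows withdrawal for adverse event or discretion in both arms, and nothing shows how often either route would be used or how the patients lost would have fared.

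**Conclusion.** The point holds as a cheap and worthwhile improvement. The protocol lets a fully dosed patient in either arm leave the study for reasons that do not preclude outcome assessment, and specifies only safety follow-up and contact attempts afterwards. Initial and definitive cure may then go uncollected and be lost from the non-inferiority test.

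The size is conditional: 0.27 or 0.80 point per unknown outcome, and up to x points either way in the difference if a share x of each arm is lost. The 1%, 4% and 5% shares and all cure rates used are assumptions. Frequency, size and direction of any bias cannot be stated from the protocol. It would go too far to say that the non-inferiority conclusion is invalid or that the trial is underpowered for this reason.

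**What to change.** 1. In Section 12.6.1, and consistently in Section 13 (Visit 1 - Day 1), Section 15.6.1 and Section 16, separate stopping the infusion from ending follow-up. Use the same wording for both arms, which means aligning Section 15.6.2 with 15.6.1.
2. End follow-up only for death, withdrawal of consent to follow-up, loss to follow-up or study termination. Treatment failures leave as already planned.
3. Keep fully dosed, unrescued patients on the scheduled Day 30/45 and 6-month assessments, omitting any procedure unsafe for the patient, such as splenic aspirate in pregnancy.
4. Record patients given another antileishmanial drug for worsening or persistent Kala-azar as not achieving definitive cure, so that later aspirates are not credited to study drug. Without this, rescued patients (Section 16.2) would have no clear outcome.
5. Follow patients whose infusion was stopped as well. Their data enter the MITT test only if the protocol-specified-duration condition in Section 20.1 is also changed; decide this explicitly.

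The cost is protocol wording in several sections, with no new visits. The downside is that sites follow a few more patients, some of them unwell, to 6 months.

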*** Lost to follow-up**

Any patient who was lost to follow-up before the 6 months visit will be withdrawn from the study.

### Procedures for handling patients who discontinue the study prematurely

Investigators should make an attempt to contact those patients who do not return for follow-up on Day 30, Day 45 (only for patients with splenic aspirate score +1 on Day 30) and 6 months after study drug administration. Information gathered should be described in the source and CRF.

### Recording Patient Withdrawals

In the event of a patient withdrawal, the following information must be recorded in the CRF:

- Date of withdrawal
- Reason for withdrawal
- Last treatment date
- Follow-up assessments

If a patient withdraws or is withdrawn from the study, he/she will be requested to return for a follow-up visit after 1 week of the withdrawal date, for recording AEs and physical examination.

The Investigator should continue to follow-up all SAEs or other AEs that are considered to be related to the study drugs, until resolved or assessed to be chronic or stable by the Investigator. This should be documented in the patient’s medical records. This follow‑up may be extended beyond the end of the study period.

In the case of patients lost to follow-up, all attempts to contact the patient must be documented in the patient’s medical records.

### Replacement of Patients Withdrawn

- None of the patients will be replaced.

# 13. COURSE OF STUDY

- Screening of patients with rK39 test and splenic aspiration will be performed to ensure that only those patients who have pathologically confirmed Visceral Leishmaniasis are enrolled in the study.
- Patients will be randomized to receive either Amphomul^®^ 15 mg/kg single dose infusion or AmBisome 15 mg/kg single dose infusion on Day 1.
- Patients will be hospitalized for duration of 7 days starting from the first dose of the study drugs.

#### Screening Visit*-*Visit 0 (Day ‑7 to Day 0)

- Screening can be done during Day ‑7 to Day 0 so that the results are available by Day 1 and the patient can be administered the study drug on Day 1.
- The patient/LAR/ impartial witness will be given information on the study and the opportunity to ask for more details. The patient/LAR/ impartial witness will be provided with the written ICF. The Investigator will ask the patient/LAR/ impartial witness whether they agree to participate. Consent will be documented, if given, and will be followed by rest of the screening procedures.
- Detailed physical examination of patients will be performed.
- Prescreening rK39 dipstick test will be done to confirm the presence of amastigotes (*Leishmania- Donovani* bodies), and if positive, this will be followed by splenic or bone marrow aspirate smear examination.
- **rK39 dipstick test:** rK39 dipstick test will be performed prior to any screening procedure The rK39 dipstick test will be performed for serological diagnosis of Visceral Leishmaniasis. This test will be conducted only at screening visit, to avoid unnecessary splenic aspiration. Kalazar Detect™ for Visceral Leishmaniasis-Rapid Test (Manufactured by InBios International, Inc) will be used. The following procedure will be performed.
- 20 μL of serum will be applied to the sample pad.
- Three drops of chase buffer provided will then be applied to the sample pad.
- Results will be read after 10 minutes.
- A red to light pink test line will indicate that the test is positive for Visceral Leishmaniasis. No test line will indicate that the test is negative. In both cases the control line should appear, if the control line is not present the test will be considered as invalid. The figure below shows a test strip that has tested positive for Visceral Leishmaniasis.

[figure not shown]

- Only patients who are rK39 positive will be evaluated for inclusion/exclusion criteria, demography and medical history.
- Findings of Visceral Leishmaniasis will be confirmed clinically and documented.
- Baseline laboratory investigations, ECG and chest X-ray will be performed to ensure that all the inclusion criteria are met. Patients will be randomized only after the investigator has assessed them for inclusion and these criteria are all fulfilled
- Detailed systemic examination of patients will be performed.
- Sufficient amount (Approximately 10 mL) of venous blood will be withdrawn, for performing following investigations:
  - Hematology:- hemoglobin, RBC, ESR, platelets, total and differential leukocyte count
  - Biochemistry:-
    - Liver function tests (Serum ALT, AST, alkaline phosphatase, total bilirubin, serum albumin, prothrombin time)
    - Renal function tests (serum creatinine, BUN*)*
    - Electrolytes (sodium, potassium, magnesium)
  - HIV test, HCV and HBsAg tests.
  - Fasting blood sugar test.
  - Parascreen antigen test for detection of malarial parasites
- X-ray chest and 12-lead ECG
- UPT (for females of child bearing potential only)
- Urine analysis (routine, microscopy )
- **Splenic aspirate**
  - Splenic aspirate will be performed to assess parasitological cure.
  - If the spleen is not palpable then Bone marrow aspirate will be done.
  - Splenic aspiration will be done only if rK39 test is positive.
  - Prothrombin time will have to be carried out before splenic aspiration and procedure will be done only if result is ≤4 seconds above the control.
  - Splenic aspirate slides will be stained by either Leishman’s stain or Giemsa stain. Both the stains contain eosin as Acidophilic Dye Component. Leishman’s stain contains Methylene Blue as Basophilic Dye Component whereas Giemsa Stain contains azure B as Basophilic Dye Component. Leishman's Stain is technically easy to perform and procedure of staining takes less time. Parasite density will be graded microscopically (X10 eyepiece X100 objective) using a logarithmic scale from +1 (1 to 10 amastigotes per 1000 oil immersion microscopic fields) to +6 (>100 amastigotes per oil immersion field). The grading will be done as follows:

| **Table 1: Grading system for grading parasite density microscopically** | |
| --- | --- |
| **Grade** | **Average parasite density** |
| +6 | >100 amastigotes/field |
| +5 | 10-100 amastigotes/field |
| +4 | 1-10 amastigotes/field |
| +3 | 1-10 amastigotes/10 fields |
| +2 | 1-10 amastigotes/100 fields |
| +1 | 1-10amastigotes/1000 fields |
| 0 | No amastigotes/1000 fields |

- Previous and concomitant medications will be recorded.
- Data obtained from the laboratory investigations will be used as soon as available to decide patient’s participation in the study.

**Visit 1-(Day 1 to Day 7)**

**Visit 1 - Day 1 (Start of study drug treatment)**

- The patients will be re-evaluated clinically.
- If all eligibility criteria are satisfied, then the patient will be included in the study to receive treatment with Amphomul^®^ or AmBisome.
- Patients not fulfilling any of the eligibility criteria on this visit would not be included in the study and labeled as screening failures.
- Laboratory investigations will be done at Investigator’s discretion.
- Permuted Block randomization with block of size 4 and ratio of 3:1 in the two groups (Amphomul and AmBisome) will be generated for each center. Patients will be randomized in the ratio of 3:1 to receive either Amphomul^®^ infusion (15 mg/kg as a single dose infusion) over 4 to 6 hours or AmBisome 15 mg/kg as a single dose infusion over 4 to 6 hours.
- Test dose consisting of 1 mg will be administered in 5% dextrose over a period of approximately 15-20 minutes prior to administration of full-dose infusion of Amphomul^®^.
- The IP (Amphomul^®^)*,* diluted (maximum dilution allowed to 1 mg/mL) in 5% dextrose will be administered as an infusion.
- Before administration AmBisome has to be diluted with 12 mL sterile water to yield a preparation containing 4 mg of Amphotericin B/mL. This diluted AmBisome will be further diluted with 5% Dextrose to a concentration not less than 1 mg/mL.
- Test dose consisting of 1 mg will be administered in 5% dextrose over a period of 10 minutes prior to administration of full-dose infusion of AmBisome
- No premedication will be administered prior to the study drug administration.
- However, if patient experiences chills or any infusion related reactions after starting infusion, concomitant medication(s) can be administered at the discretion of the investigator.
- As for use of all Amphotericin B products, facilities for cardiopulmonary resuscitation will be kept readily at hand when administering the drug due to possible occurrence of anaphylactic reactions.
- In case of severe hypersensitivity reactions uncontrolled by the premedications or cardiopulmonary complications of hypersensitivity, the patient would be discontinued from the study and would be treated for the complications till the patient becomes stable.
- The patient will be closely monitored for approximately 6 hours following the completion of infusion for any IRTs.
- Vital signs will be recorded.
- After the study drug administraton, patient will be daily monitored for any AEs and SAEs, which will be carefully recorded in the patient’s medical records and CRF.
- Previous and concomitant medications will be recorded.
- DLT assessment will be performed

